#### Patient harm instances

A general practitioner from each intervention group practice will conduct two patient chart audits using the TRM over the course of the intervention period. A summary of the findings of each audit (i.e. triggers identified, number of instances of undetected patient harm identified, severity of each instance of harm detected, potential avoidability or preventability of each instance of harm detected, and description of action resulting from audit) will be provided to researchers. These data will provide an indicator of the potential efficacy of the TRM in identifying undetected instances of patient harm and its usefulness.

### Data management and analysis

As this is a feasibility study, statistical analyses will be primarily descriptive, as recommended in best practice guides for pilot and feasibility studies [29, 32]. A descriptive report of the mean change in the scores on each of the scales of the GP-SafeQuest pre- and post- intervention for the intervention and control groups will be produced alongside a measure of the range of these scores. Each participating GP practice will be given a code. The code key will be encrypted and stored separately from the database of questionnaire responses. As the individual respondents will be tracked using subject-generated identification codes, the individual level data will be anonymous.

The qualitative data emerging from the post-intervention semi-structured interviews will be analysed using the framework method for qualitative data analysis in accordance with best practice [33]. Each interview participant will be given a code. The code key will be encrypted and stored separately from the interviews. Following transcription, the interview recordings will be destroyed. Both the questionnaire and interview transcripts will be stored on a password-protected computer. The data will be stored at NUI Galway, and only the researchers will have access.

### Dissemination policy

The findings from the study will be published as a journal paper and presented at an international primary care conference. The findings will also be disseminated via the internet at www.primarycaretrials.ie and through social media.

## Discussion

This study will investigate the impact of an intervention, derived from the SPSP-PC, on the safety climate of primary care practices. We will investigate if this intervention, comprising safety climate measurement and feedback using the GP-SafeQuest and patient chart audit using the trigger review method, results in changes in safety climate among intervention group general practices as compared to the control group and aids with the detection and remediation of instances of patient harm. As this is a feasibility study, process evaluation will form the core outcome measure allowing for an assessment of the potential efficacy, utility, acceptability, and sustainability of the intervention in Irish primary care settings and the anticipation of potential pitfalls of a future randomised controlled trial (e.g. low recruitment rates, attrition, low rates of completion of measures). Given the high usage of primary care services, and the rates of errors or instances of undetected patient harm reported in primary care in other countries [16, 17], it is anticipated that the intervention in the current study will provide useful data surrounding the prevalence of undetected patient harm in Irish primary care and the safety climate of Irish general practices.

There are a number of strengths of this study. There is a noted gap in the research literature surrounding the assessment of, and intervention to improve, safety climate in primary care settings [3, 10–12], particularly in countries outside of the UK, USA, and Australia [28, 34]. The current study will assess, and intervene upon, safety climate in Irish primary care settings providing novel and interesting data. Further, the study involves the delivery of an intervention for which initial evaluative data emerging from Scotland have been positive [11] but which requires additional empirical evaluation and validation. However, the likelihood of intervention success is improved by the validation of the individual interventional components (i.e. the safety climate measure and the TRM) in previous research studies [15, 22–25, 35]. Finally, the use of a mixed methods approach may also be considered a strength of the study. Verbakel and colleagues [3] have previously noted the complexity of multi-component patient safety interventions designed for implementation in primary care settings. A mixed methods approach is therefore suitable in order to capture participant experiences and valuable qualitative data to contribute to process evaluation and inform a future, larger trial of the intervention.

There are also a number of limitations to the planned study. First, there is a potential for selection bias to occur as practices that are invited to participate either opt-in or opt-out. In this way, practices in which there is a greater focus on patient safety, and consequently an increased motivation to implement interventions to improve patient safety, may be more likely to choose to partake in the proposed study and this may impact upon intervention outcomes. Second, there is also a reliance on self-report in the current study (i.e. self-report of safety climate, self-report of incidents of patient harm identified) rather than objective data. However, due to the nature of the variables under measurement (i.e. perceptions of safety climate, incidents of harm detectable only through the review of confidential patient information), it is not feasible to plan to collect more objective data.

The planned research programme will contribute to existing knowledge by evaluating an emerging intervention for patient safety in the context of Irish primary care settings. The resulting data may inform our knowledge of the frequency of patient safety incidents in primary care and contribute to an improved standard of care delivered by general practitioners.

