## Abstract

**Background:**

Research on patient safety has focused largely on secondary care settings, and there is a dearth of knowledge relating to safety culture or climate, and safety climate improvement strategies, in the context of primary care. This is problematic given the high rates of usage of primary care services and the myriad of opportunities for clinical errors daily. The current research programme aimed to assess the effectiveness of an intervention derived from the Scottish Patient Safety Programme in Primary Care. The intervention consists of safety climate measurement and feedback and patient chart audit using the trigger review method. The purpose of this paper is to describe the background to this research and to present the methodology of this feasibility study in preparation for a future definitive RCT.

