**Methods:**

The SAP-C study is a feasibility study employing a randomised controlled pretest-posttest design that will be conducted in 10 general practices in the Republic of Ireland and Northern Ireland. Five practices will receive the safety climate intervention over a 9-month period. The five practices in the control group will continue care as usual but will complete the GP-SafeQuest safety climate questionnaire at baseline (month 1) and at the terminus of the intervention (month 9). The outcomes of the study include process evaluation metrics (i.e. rates of participant recruitment and retention, rates of completion of safety climate measures, qualitative data regarding participants’ perceptions of the intervention’s potential efficacy, acceptability, and sustainability), patient safety culture in intervention and control group practices at posttest, and instances of undetected patient harm identified through patient chart audit using the trigger review method.

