### Objectives

In spite of the high costs of medical errors in Northern Ireland [26] and the Republic of Ireland [27], there is a notable dearth of published research investigating interventions to improve safety climate or culture in primary care settings [3], particularly in countries outside of the USA, UK, and Australia [28]. The planned study is thus designed to address this research gap. The primary objective of this study is to inform the planning of a definitive randomised controlled trial by providing evidence on whether the intervention is feasible, useful, and sustainable in the Irish context, by determining the rates of recruitment and completion of the outcome measures and by exploring the acceptability of the intervention to study participants. A secondary objective is to allow an estimate of an appropriate sample size to be calculated to ensure that a possible future definitive trial is adequately powered. Therefore, while the outcomes of the intervention for the safety climate of the participating practices are of interest, the evaluation of the process of its implementation is the primary aim.

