#### Safety climate

In addition to functioning as a diagnostic learning tool, the GP-SafeQuest measure of safety climate employed in the current study will also be used to evaluate the impact of the intervention. For the intervention group practices, it will be possible to track changes in safety climate across the measurement time points (i.e. baseline, study midpoint, and study terminus). The comparison of safety climate at the study’s terminus (posttest time point) within intervention group practices and control group practices will also allow for an evaluation of the impact of the intervention. Finally, the effect sizes observed here (i.e. any change in mean safety climate scores as a result of the intervention or any difference in mean safety climate scores at posttest between the intervention and control groups) will also contribute to the planning of a future definitive trial. This knowledge of an observed effect size in the feasibility study will be considered along with the feasibility of detecting different levels of effect sizes and the real-world importance of the various effect sizes, when setting a desired effect size for the definitive study and determining an appropriate sample size.

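### The article says the between-arm comparison of safety climate will evaluate impact, but the descriptive results planned from five versus five practices could inform only on very large effects

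*Protocol article*

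**What the plan says.** Two places in the protocol article give the safety climate comparison a causal purpose. The Discussion says the study will investigate whether the intervention "results in changes in safety climate among intervention group general practices as compared to the control group". Under Outcome measures, the Safety climate section says that comparing the two groups at study end "will also allow for an evaluation of the impact of the intervention". The same section names the observed change, or the observed posttest difference between groups, as one input to planning the definitive trial, alongside feasibility and real-world importance.

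The section on data management and analysis says that "statistical analyses will be primarily descriptive", because this is a feasibility study. The one safety climate summary it specifies is the mean change on each GP-SafeQuest scale in each arm, with a measure of range.

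On size, the abstract describes a study "that will be conducted in 10 general practices in the Republic of Ireland and Northern Ireland". Half of these are assigned to the intervention for nine months; of the other half the abstract says: "The five practices in the control group will continue care as usual".

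On purpose, the Objectives say that "the evaluation of the process of its implementation is the primary aim".

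**The concern.** Whether the intervention changes safety climate relative to control is a question about a between-arm difference. Answering it needs an estimate of that difference and a measure of its uncertainty. The plan offers mean changes by arm, ranges, and observed differences. A range reflects how far apart the extreme scores lie. It tends to widen as respondents are added, whereas the uncertainty of a difference shrinks as practices are added, so it cannot stand in for an interval.

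The article therefore credits the comparison with a property that the stated analysis does not have. At stake is what this study may conclude about the intervention. Two bare means reported under an aim of evaluating impact leave the reader unable to see that a difference in either direction could easily be chance. The limitations in the Discussion cover selection bias and self-report but do not say that the study cannot judge effect.

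**Working it through.** **Plan's own figure.** The article gives no power, significance level, SD, ICC or target effect, so there is no calculation to reproduce. The counts agree: 8 practices in the Republic of Ireland plus 2 in Northern Ireland make 10. Reading the randomisation section as equal allocation within each jurisdiction gives 4 v 4 and 1 v 1, hence 5 v 5.

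**Inputs.** From the article: practices are randomised, five per arm. Assumed, because the article does not give them: two-sided 5% level, 80% power, m = 5 to 20 respondents per practice, ICC = 0.05 to 0.30, no baseline adjustment.

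**Step 1: precision with practices as the unit.** Let S be the SD of the practice-level value analysed.
- Standard error of the difference = S × √(2/5) = 0.632 S.
- Degrees of freedom = 10 − 2 = 8; t(0.975, 8) = 2.306.
- 95% half-width = 2.306 × 0.632 S = 1.46 S.
- With jurisdiction in the model (7 df, t = 2.365) the multiplier is 2.365 × 0.632 = 1.50, applied to the residual SD.

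**Step 2: power from the noncentral t, 8 df.**

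| True difference (in S) | Power |
|---|---|
| 0.5 | 11% |
| 0.8 | 20% |
| 1.0 | 29% |
| 1.5 | 55% |
| 2.0 | 79% |

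The difference detectable with 80% power is 2.02 S.

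**Step 3: individual-SD units for unadjusted posttest means.** S = √(ICC + (1 − ICC)/m).
- Most favourable (m = 20, ICC 0.05): S = √(0.05 + 0.95/20) = 0.312. Half-width 1.46 × 0.312 = 0.46; detectable difference 2.02 × 0.312 = 0.63.
- Least favourable (m = 5, ICC 0.30): S = √(0.30 + 0.70/5) = 0.663. Half-width 1.46 × 0.663 = 0.97; detectable difference 2.02 × 0.663 = 1.34.

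**Step 4: what bare means could show.** Take m = 10 and ICC 0.05 to 0.20. S is 0.381 to 0.529, and the standard error is 0.241 to 0.335 individual SD.
- With no true effect, the chance that the intervention arm looks better by at least 0.2 SD is 1 − Φ(0.2/0.241) = 20% to 1 − Φ(0.2/0.335) = 28%.
- With a true gain of 0.3 SD, the chance that it looks no better is Φ(−0.3/0.241) = 11% to Φ(−0.3/0.335) = 19%.

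**Baseline.** Steps 1 and 2 apply equally to practice-level mean change if S is the SD of those changes. Steps 3 and 4 do not carry over directly. With equal variances, the variance of a change is 2(1 − ρ) times that of a posttest mean, where ρ is the unknown practice-level correlation between baseline and posttest, so simple change is more precise only if ρ exceeds 0.5. Covariate adjustment for baseline would narrow the figures by an amount that cannot be known from the article.

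**The case against.** The strongest reply is that the article already limits itself. It calls itself a feasibility study throughout, makes process evaluation the primary outcome, and gives feasibility as the reason for descriptive analysis. Directly after the quoted Discussion sentence it returns to process evaluation as the core measure and speaks of potential efficacy. All of this stands, and it is why the point is minor. It does not remove the two sentences that assign an evaluation of impact to the comparison, and nothing in the article says that the study cannot judge effect.

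A second reply is that interval methods are commonly left to a full protocol or SAP. That is fair, and the absence of such detail is not the finding. The finding is the mismatch between a stated causal purpose and the stated results. No choice of method in another document would make five practices per arm informative on small or moderate effects.

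Several stronger readings are tempting, and the article does not support them:
- **That no between-arm comparison is planned.** The plan is primarily, not solely, descriptive, and the observed posttest difference is to be used as an effect size.
- **That no effect at all could be detected.** A difference of about 2 SD of practice means could be. Under allocation within jurisdictions there are 70 × 2 = 140 possible allocations, so even a permutation test could reach p = 2/140 = 0.014.
- **That the abstract claims effectiveness for this study.** The subject of the sentence saying it "aimed to assess the effectiveness of an intervention derived from the Scottish Patient Safety Programme in Primary Care" is the wider research programme, and the same paragraph places the definitive RCT in the future.
- **That the result would drive adoption or abandonment.** The article contains no such rule; the use it states for the observed effect is planning.

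**Conclusion.** The concern holds as a minor point about what the study may conclude. The impact wording in the Safety climate section and the Discussion goes further than the planned results can carry. With five practices per arm those results cannot support or exclude any but very large effects: a half-width of about 1.5 SD of practice means and a detectable difference of about 2.0 SD. These two figures rest only on 5 v 5 practices, a t-based analysis with 8 df, and conventional error rates. The translation to roughly 0.6 to 1.3 individual SD (half-width about 0.5 to 1.0) also rests on assumed respondent numbers and ICC and on unadjusted means.

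A reader might infer that the study is too small or that descriptive analysis is the wrong choice. Neither follows: both suit a feasibility study with a process outcome as primary, and no increase in the number of practices is called for.

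**What to change.** 1. In the Safety climate section and the Discussion, state that change in safety climate will be described and estimated to inform planning, and that no conclusion on effectiveness will be drawn.
2. In the section on data management and analysis, add to the range, for each scale, the between-arm difference in practice-level mean change with a 95% confidence interval that takes practices as the unit (8 df, or 7 df if jurisdiction is included).

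The abstract's sentence on the research programme can stay as it is.

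The cost is a few sentences and one interval for each of the five scales, with no new data or practices. The stated aim becomes more modest and the intervals will be wide, which correctly reflects what ten practices can show.

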## Abbreviations

NHS: National Health Service
SAP-C: Safety climate in primary care
SPSP-PC: Scottish Patient Safety Programme in Primary Care
TRM: Trigger review method
UK: United Kingdom
WestREN: Western Research Network
